This study is a prospective interventional study with minimal risks and constraints, not involving health products, according to the following points: "1. random allocation of procedure(s), or diagnostic or medical strategies or intervention(s) of current practice to a person or a group of persons" and "11. Interviews, observations and questionnaires, the results of which, in accordance with the protocol, may lead to changes in the participant's usual medical care and which therefore do not fall within the scope of the research mentioned in 3° of Article L.1121-1 of the Public Health Code" of the Order of 12 April 2018 establishing the list of research mentioned in 2° of Article L.1121-1 of the Public Health Code.

This study is a preventive study which forms part of the 6 fundamental skills of family practice*.*

The investigators are practitioners active in the field of primary care and networking ([name] [name], head of the university department of family practice in Brest):

- [name] heads an EA focusing on the study of Primary Care and Prevention in the general population (SPURBO) and has published a large amount of research on this subject.
- [name] has led a number of behaviour change groups at the diabetes network in Orléans and is an expert in motivational interviewing training.

These investigators, qualified persons in accordance with article 1122-1 of the Public Health Code, will be represented by family practice interns who will collect consent and data. These interns will be qualified persons under article 1122-1 of the Public Health Code, as they will have received appropriate training in the research protocol, as well as training in Good Clinical Practice and the use of the observation notebook, all under the aegis of the doctor-investigators and the Clinical Research and Innovation Delegation, which is ISO 9001-2015 certified for its activities in promoting and coordinating academic interventional clinical trials.

- 1. Primary endpoint

Comparison of the mean Non Laboratory Interheart risk score between the two arms at 24 months.

- 1. Secondary end points

Those secondary clinical endpoints will be measured at 24 months:

- Quality of life assessed by the WHOQOL brief scale,
- BMI reduction,
- Level of smoking (Reduction in the number of smokers/reduction in the number of cigarettes per smoker)
- Improving nutrition using the DASH Q,
- Level of physical activity using the IPAQ questionnaire,

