These clinical criteria consist of :

- Quality of life assessed by the WHOQOL brief scale,
- Weight, height and BMI,
- Smoking levels (reduction in the number of smokers/reduction in the number of cigarettes per smoker)
- Nutrition using the DASH Q questionnaire,
- Level of physical activity using the IPAQ short questionnaire,
- Alcohol consumption by collecting declared weekly alcohol consumption

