Participants will participate in the study for three years.

- 1. Support for research

There is no standard management of primary prevention patients in the community. The specific research management was created on the basis of the results of a structured review of the literature on the best current recommendations for good practice in primary care, adressing an adapted diet, adapted physical activity, reduction or cessation of smoking and alcohol, and weight loss.

- 1. Withdrawals
     1. Withdrawal of participants

Participants may withdraw their consent and ask to leave the study at any time and for any reason. In the event of premature withdrawal, the investigator must document the reasons as fully as possible.

The investigator may temporarily or permanently discontinue a participant’s participation in the study for any reason that is in the best interests of the participant, particularly in the case of serious adverse events.

If a participant is lost to follow-up, the investigator will make every effort to contact the person again*.*

- - 1. Total or partial arrest of the study

Unforeseen events or new information relating to the research, in the light of which the objectives of the study are unlikely to be achieved, may lead the sponsor to interrupt the study prematurely.

The CHRU de Brest reserves the right to discontinue the study at any time if the inclusion objectives are not met.

1. Safety assessment

As part of this study, investigators will report research-related adverse events occurring during the participation of recruited patients via the electronic CRF. The sponsor will receive an e-mail alert whenever an AE is entered into this CRF. This information will be used to create a register which will be used to draw up the final study report.

In accordance with the Public Health Code, new facts (defined in 12° of article R1123-46) will be reported to the CPP.

1. Statistics

Responsible for analysis: UGD - Brest Clinical Research and Innovation Delegation - CHRU de Brest - [name]

All analyses were carried out using SAS and R software.

Analyses will be carried out with an alpha risk of 0.05

- 1. Description of planned statistical methods,

The general principles of the analysis are :

- The analysis will be conducted on "intention to treat".
- There is no intermediate analysis because there is no biomedical risk associated with the research.

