  - Hierarchical analysis in two steps: 1) comparison of the mean Interheart between the two arms at a risk of alpha=0.05, then in the event of a statistically significant result 2) comparison of the 6 secondary endpoints between the two arms, using the Holm-Bonferroni correction to take account of the multiple comparisons carried out in this step. In accordance with the principles of hierarchical analysis, the tests in step 2) can only be performed demonstratively if the test in step 1) is statistically significant (p<0.05).
- Quantitative endpoints will be compared between the two arms using a Student's t test. Qualitative endpoints will be compared between the two groups using a Chi-2 test. Multivariate analyses will be performed secondarily using a linear model to adjust for potential confounding factors.
  1. Expected number of people to be included in the research, and expected number of people in each research location with statistical justification

The calculation of the number of participants is based on the comparison of the mean Interheart between the two arms: for a power of 80%, a risk alpha=0.05 and an effect size (mean difference / standard deviation) of 0.20 the number of participants required is 394 per arm. Including approximately 20% lost to follow-up, a total of 985 participants should be included. With a number of participants of 394 patients per arm and the assumption of an effect size of 0.20 for each secondary endpoint, the test power is approximately 68% for each secondary endpoint using the Holm-Bonferroni correction to account for multiple comparisons.

- 1. Method for taking into account missing, unused or invalid data

Missing data will be identified via the electronic CRF, and the investigators will be called back to complete the data. Incomplete files will be declared lost to follow-up.

1. Right of access to data
   1. Access to data

In accordance with GCP :

- the sponsor is responsible for obtaining the agreement of all parties involved in the research in order to guarantee direct access to all research sites, source data, source documents and reports for the purposes of quality control and audit by the sponsor,

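### Secondary endpoints mix change and level wording, and the main t test ignores the time-zero value; a baseline-adjusted comparison settles both at no cost

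*Protocol*

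**What the plan says.** Section 4.3 lists six secondary clinical endpoints, to be measured at 24 months. The wording is not uniform. BMI is "BMI reduction" and diet is "Improving nutrition using the DASH Q". Physical activity is a level, alcohol is declared weekly consumption, quality of life is a scale, and smoking uses both level and reduction in one line.

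Section 6.2.1 lists what the research team measures in every participant, whatever the arm, at time zero and at 6, 12, 18 and 24 months. There BMI is "Weight, height and BMI" and diet is "Nutrition using the DASH Q questionnaire"; smoking still carries the word reduction.

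Section 8.1 tests the six endpoints after a significant primary result, with Holm-Bonferroni correction. Quantitative endpoints are compared by Student's t test. Linear models come second, to adjust for potential confounders. Section 8.2 gives "an effect size (mean difference / standard deviation) of 0.20 the number of participants required is 394 per arm" for the primary endpoint and, for the secondary ones, "the assumption of an effect size of 0.20 for each secondary endpoint, the test power is approximately 68% for each secondary endpoint".

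**The concern.** The six endpoints form a multiplicity-controlled family from which the protocol intends to draw formal conclusions, so the variable entering each test is part of the endpoint's definition. For BMI and diet the wording of section 4.3 leans towards a change, the heading of the list points to the 24-month value, and the t test of section 8.1 would comply with either.

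Both choices estimate the same difference between randomised arms, so validity is not at stake. Precision is, and with it the verdict on a given data set. Which choice is sharper depends on how strongly the endpoint tracks over two years: the change is the weaker variable when tracking is poor, the 24-month value when tracking is strong. Because Holm is sequential, a verdict on one endpoint also moves the thresholds for the others. Neither t test makes the best use of time-zero values that are collected anyway.

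**Working it through.** **Inputs.** From the protocol: 394 per arm, standardised effect 0.20, six endpoints, Holm-Bonferroni (sections 8.1 and 8.2); "Analyses will be carried out with an alpha risk of 0.05" (section 8). Assumed: two-sided tests (sidedness is not stated, but two-sided reproduces the figures); independent endpoints unless noted; equal standard deviations at both visits; r, the correlation between time-zero and 24-month values, of 0.3, 0.5 or 0.8. The protocol gives no r.

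**Step 1: the plan's own figures.** A two-sided t test at 0.05 with 80% power and effect 0.20 needs 393.4, so 394 per arm. Then 2 × 394 = 788 and 788 / 0.80 = 985, as stated. Simulating Holm over six tests, all at 0.20 with 394 per arm, gives a power per endpoint of 68.5% if the endpoints are independent, 67.7% at a correlation of 0.3 between them and 67.2% at 0.5. The stated 68% reproduces. Plain Bonferroni at 0.05/6 would give 56.7%, so the figure is indeed a Holm figure.

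**Step 2: does 68% depend on change or level?** The calculation takes in only mean difference divided by standard deviation. If 0.20 is assumed on the tested variable, power is about 68% whichever variable that is.

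**Step 3: what the unnamed standard deviation leaves open.** With standard deviation S at each visit, the change has standard deviation S × √(2(1 − r)). A raw difference of 0.20 S is therefore an effect of 0.20 / √(2(1 − r)) on the change scale. In a model with the time-zero value as covariate the residual standard deviation is S × √(1 − r²), so the effect is 0.20 / √(1 − r²). Holm power for one such endpoint, the other five at 0.20:

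| r (assumed) | t test, 24-month value | Effect on change | t test, change | Effect, adjusted | Adjusted model |
|---|---|---|---|---|---|
| 0.3 | 69% | 0.169 | 52% | 0.210 | 73% |
| 0.5 | 69% | 0.200 | 69% | 0.231 | 82% |
| 0.8 | 69% | 0.316 | 98% | 0.333 | 99% |

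The two t tests coincide at r = 0.5, where 2(1 − r) = 1.

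**Step 4: why the adjusted model is never worse in large samples.** The variance factors are 1 for the 24-month value, 2(1 − r) for the change and 1 − r² for the adjusted comparison. 1 − r² cannot exceed 1. Since 1 − r² = (1 − r)(1 + r) and 1 + r ≤ 2, it cannot exceed 2(1 − r) either. With the time-zero value as covariate, entering the 24-month value or the change as outcome gives the same arm coefficient, so the level-or-change question disappears.

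**Step 5: could the two t tests disagree on one data set?** With a true difference of 0.20 S and both tests at 0.05/6, simulation gives opposite verdicts in about 42% of trials at r = 0.8. This too rests on the assumed r.

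**The case against.** A reader might infer that 68% cannot hold under both a change and a level definition. The protocol does not support that. The figure is stated conditionally on a standardised effect and follows on whichever scale the 0.20 is placed. The two scales part only if one raw difference is fixed and r differs from 0.5, and the protocol gives neither.

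A reader might also infer that sections 4.3 and 6.2.1 hold rival definitions. They do not. The list in section 6.2.1 is what is measured at each visit, starting at time zero, when no reduction can yet exist. A reduction would be derived from those measurements. That list also keeps reduction wording for smoking, so neither section is uniformly level or change.

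It is further fair to say that reduction and improving may only name the hoped-for direction, that section 4.3 never mentions a change score, and that the choice between final value and change is often left to a statistical analysis plan, which is not at hand. These points stand, and they keep the matter small. They do not remove it: the uneven wording is in the protocol's own endpoint list, and section 8.1 does fix the main test as unadjusted and places linear models second.

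Finally, quoting 68% beside an adjusted analysis describes a test that is no longer the main one. That is acceptable if it is labelled as unadjusted and therefore conservative.

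**Conclusion.** The point holds as a free improvement. The wording of section 4.3 is uneven, the t test of section 8.1 fits either reading, and section 8.2 does not name the standard deviation behind its 0.20. There is no arithmetic error: 394 per arm, 985 in total and 68% all reproduce.

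The gain from adjustment, for one endpoint with a difference of 0.20 standard deviations of the 24-month value, is from about 69% to about 73%, 82% or 99% at r = 0.3, 0.5 or 0.8. It rests on the assumed r, equal standard deviations, independent endpoints, the other five at 0.20, and 394 analysed per arm. Like the plan's 68%, it leaves out the chance of passing the primary test.

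It would be too strong to say that the choice makes a test nearly certain or nearly hopeless. A power as low as 30% at r = 0.8 appears only if 0.20 is instead placed on the change and the 24-month value is tested. That is the opposite premise to the one behind 98% for the change, so the two figures do not describe the same data.

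**What to change.** - **Section 4.3:** define each quantitative secondary endpoint as the value at 24 months, and drop reduction and improving from the definitions, or state them only as the expected direction.
- **Section 8.1:** make the main comparison of each quantitative secondary endpoint a linear model with arm and the participant's own time-zero value. The Holm-Bonferroni procedure, its place after the primary test and the Chi-2 test for qualitative endpoints stay as they are.
- **Section 8.2:** say that 0.20 is in standard deviations of the 24-month value, and that 68% is the figure without baseline adjustment and hence conservative for the adjusted analysis.

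The cost is wording only. The time-zero values are already collected in both arms under section 6.2.1, section 8.1 already foresees linear models, and neither the sample size nor the visit schedule changes.

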6.2.2. The Control group

In the control group, people with a moderate CVDR will receive brief advice according to their Interheart score.

The brief advice provided during screening will be standardised minimum advice in line with the latest recommendations and will be identical in the two steps. It will include the health messages disseminated to the general public by the national plans identified during the situational analysis carried out at the start of the project (Programme national de réduction du tabagisme (PNRT); Programme national nutrition santé (PNNS); Plan Santé sport bien-être (SSBE); Plan national santé environnement (PNSE); Plan de santé au travail; Plan Accident Vasculaire Cérébral (Plan AVC); Plan Obésité).

Example: *« You have declared that you are an active smoker. Quitting smoking will reduce your risk of cardiovascular disease. You have stated that you do not eat enough fruit and vegetables. Eating fruit and vegetables every day will reduce your risk of cardiovascular disease. »*

6.2.3. The Intervention group

6.2.3.1 Inclusion

In the intervention group, people with moderate CVDR will receive brief advice followed by a multi-behavioural intervention adapted to local resources.

The intervention was defined on the basis of a systematic review of international and national good practice recommendations for cardiovascular prevention.

The diet will follow the Dash Diet recommendations.

The reduction of tobacco and alcohol consumption will be proposed.

Increased physical activity will be recommended as a combination of aerobic and resistance activity.

There is no provision for compensation for people included in the intervention group. A review of the literature shows that financial incentives are not effective when used alone. On the other hand, when they are combined with a multimodal intervention, their effect is moderate and ceases when the funding is stopped (21). The aim of our project is to ensure that the intervention lasts beyond the end of the project. Secondly, financial incentives belong to a different category of the behaviour change taxonomy from that currently adopted by the SPICES consortium (including goal setting, problem solving and action planning) (22). This incentive would change the method of our intervention and create a divergence from the projects of the other members of the SPICES consortium.

6.2.3.1. Study follow-up for participants

In addition to contacts at 6, 12, 18 and 24 months, the psychological risks associated with the intervention will be collected with a specific question: "Did the participants experience any psychological effects associated with the research?

- 1. Study process

Each intervention group will hold an initial research action meeting between people with moderate CVDR and community leaders.

The aim of this meeting is to map external resources in the COB region that help the improvement of modifiable risk factors (sports associations, for example).

Each group will then meet regularly, face-to-face and/or remotely (by telephone or videoconference), under the aegis of the community champions, to work on the changes in each participant's risk factors. The one-hour sessions will be scheduled every fortnight for 2 months, then every month for 2 months, then every 3 months until the end of the study (13 sessions). These sessions will be behaviour change sessions, focusing on goal setting, action planning and problem solving. The community champions will lead these sessions and use motivational interviewing techniques.

Community champions will first take part in a 2-day training course with national experts (run in France by UNAFORMEC, a certified training association).

The community champions will be compensated for their time on a lump-sum basis. This is consistent with the interventions proposed by the other partners in the SPICES consortium.

At the same time as these sessions, the people in the intervention group will be contacted individually (face-to-face or remotely by telephone or videoconference) by the research team. The aim of this contact will be to help them make lifestyle changes to improve primary cardiovascular prevention.

The volunteer community champions will be supported by family medecine interns under the supervision of the research team. These family medecine interns of the Faculty of Brest will be working on this project as part of their mandatory master thesis. They will support the community champions, offering them logistical assistance (organising face-to-face or remote meetings), help in running their meetings and assisting the members of their groups to change their lifestyles in favour of better cardiovascular prevention.

At 6, 12, 18 and 24 months, various criteria will be measured by the research team:

- Quantitative implementation assessment criteria :
- Number of people screened, number categorised as green, orange and red.
- Number of people taking part in SPICES activities (the count will be made at the first SPICES meeting)
- Number of people carrying out the entire SPICES intervention (75% of all meetings)
- Cost of the intervention, taking into account the cost of initial training for screeners and community champions, equipment (tablets for screening and paper tools for community champions), group room hire costs, mileage allowance for community champions, an estimate of remuneration for community champions based on the minimum hourly wage and mileage allowance for participants in the intervention group.
- Qualitative implementation assessment criteria:
- The aim of collecting these criteria is to identify the barriers and facilitators to the intervention. It is based on a qualitative assessment of the screeners, the intervention and the resource people, in line with the recommendations of the Re-Aim model.
- Qualitative evaluation of screeners using focus-group methods and individual semi-structured interviews. A purposive sampling of screeners will be carried out. This will be based in particular on age, the number of people screened and the geographical location of the screening. Data collection will continue until the data is theoretically saturated. Data analysis will use a thematic analysis. Two researchers will analyse the data blindly and then collate the analyses.
- Qualitative evaluation of community champions using focus group methods and individual semi-structured interviews. A purposive sampling of community champions will be carried out. It will be based in particular on age and the geographical location of the sessions. Data collection will continue until the theoretical saturation point is reached. Data analysis will use a thematic analysis.. Two researchers will analyse the data blindly and then collate the analyses.
- Qualitative assessment of participants using focus group methods and individual semi-structured interviews. A purposive sampling of participants will be carried out. It will be based in particular on age and the geographical location of the sessions. Data collection will continue until the data is theoretically saturated. Data analysis will use a thematic analysis. Two researchers will analyse the data blindly and then collate the analyses.
- Qualitative assessment of non-participants using semi-structured individual interviews. Non-participants are defined as people who have been screened but have been lost to follow-up or have disappeared during the intervention. A purposive sampling of non-participants will be carried out. It will be based in particular on age and the geographical location of the sessions. Data collection will continue until the theoretical saturation point is reached. Data analysis will use a thematic analysis. Two researchers will analyse the data blindly and then collate the analyses.
  1. Identifying the data collected in the observation notebook

Data collected will include demographics, history, weight, height, BMI of participants, responses to Interheart questionnaires, Whoqol brief quality of life, IPAQ short physical activity, DASH-Q diet, self-reported level of smoking and self-reported level of alcohol consumption.

Demographics :

- Age
- Tobacco consumption according to Interheart (never smoked, former smoker, smoker of 1 to 5 cigarettes a day, 6 to 10 cigarettes a day, 11 to 15 cigarettes a day, 16 to 20 cigarettes a day, more than 20 cigarettes a day)
- Passive smoking, formulated according to Interheart
- Diet according to Interheart criteria (5 questions) and DASH-Q criteria (11 questions)
- Quality of life using the short Whoqol scale, 26 items exploring 4 areas: physical health, mental health, social relationships and the environment.
- Physical activity based on Interheart and IPAQ-short data (7 questions)

History

Family history: history of heart attack in fathers or mothers

Personal history: existence of type 2 diabetes, arterial hypertension, etc.

Clinical data :

- Weight, height and BMI of intervention participants
- Waist to hip ratio measured with a tape measure according to Interheart recommendations
- Professional and personal stress formulated according to Interheart
- Depression and related syndromes as formulated by Interheart
- Specific risk assessment question: did the participant experience any psychological effects related to the research?
  1. Expected duration of participation and description of duration of all trial periods, including follow-up, if applicable

The duration of screening and inclusion in the intervention and control groups will be one year.

The intervention will last two years.

The total duration of the intervention (screening + intervention) will be three years.

Participants will participate in the study for three years.

- 1. Support for research

There is no standard management of primary prevention patients in the community. The specific research management was created on the basis of the results of a structured review of the literature on the best current recommendations for good practice in primary care, adressing an adapted diet, adapted physical activity, reduction or cessation of smoking and alcohol, and weight loss.

- 1. Withdrawals
     1. Withdrawal of participants

Participants may withdraw their consent and ask to leave the study at any time and for any reason. In the event of premature withdrawal, the investigator must document the reasons as fully as possible.

The investigator may temporarily or permanently discontinue a participant’s participation in the study for any reason that is in the best interests of the participant, particularly in the case of serious adverse events.

If a participant is lost to follow-up, the investigator will make every effort to contact the person again*.*

- - 1. Total or partial arrest of the study

Unforeseen events or new information relating to the research, in the light of which the objectives of the study are unlikely to be achieved, may lead the sponsor to interrupt the study prematurely.

The CHRU de Brest reserves the right to discontinue the study at any time if the inclusion objectives are not met.

1. Safety assessment

As part of this study, investigators will report research-related adverse events occurring during the participation of recruited patients via the electronic CRF. The sponsor will receive an e-mail alert whenever an AE is entered into this CRF. This information will be used to create a register which will be used to draw up the final study report.

In accordance with the Public Health Code, new facts (defined in 12° of article R1123-46) will be reported to the CPP.

1. Statistics

Responsible for analysis: UGD - Brest Clinical Research and Innovation Delegation - CHRU de Brest - [name]

All analyses were carried out using SAS and R software.

Analyses will be carried out with an alpha risk of 0.05

- 1. Description of planned statistical methods,

The general principles of the analysis are :

- The analysis will be conducted on "intention to treat".
- There is no intermediate analysis because there is no biomedical risk associated with the research.
  - Hierarchical analysis in two steps: 1) comparison of the mean Interheart between the two arms at a risk of alpha=0.05, then in the event of a statistically significant result 2) comparison of the 6 secondary endpoints between the two arms, using the Holm-Bonferroni correction to take account of the multiple comparisons carried out in this step. In accordance with the principles of hierarchical analysis, the tests in step 2) can only be performed demonstratively if the test in step 1) is statistically significant (p<0.05).
- Quantitative endpoints will be compared between the two arms using a Student's t test. Qualitative endpoints will be compared between the two groups using a Chi-2 test. Multivariate analyses will be performed secondarily using a linear model to adjust for potential confounding factors.
  1. Expected number of people to be included in the research, and expected number of people in each research location with statistical justification

The calculation of the number of participants is based on the comparison of the mean Interheart between the two arms: for a power of 80%, a risk alpha=0.05 and an effect size (mean difference / standard deviation) of 0.20 the number of participants required is 394 per arm. Including approximately 20% lost to follow-up, a total of 985 participants should be included. With a number of participants of 394 patients per arm and the assumption of an effect size of 0.20 for each secondary endpoint, the test power is approximately 68% for each secondary endpoint using the Holm-Bonferroni correction to account for multiple comparisons.

- 1. Method for taking into account missing, unused or invalid data

Missing data will be identified via the electronic CRF, and the investigators will be called back to complete the data. Incomplete files will be declared lost to follow-up.

1. Right of access to data
   1. Access to data

In accordance with GCP :

- the sponsor is responsible for obtaining the agreement of all parties involved in the research in order to guarantee direct access to all research sites, source data, source documents and reports for the purposes of quality control and audit by the sponsor,

- the investigators will make available to the persons responsible for monitoring, quality control or auditing the research, the documents and individual data strictly necessary for this control, in accordance with the legislative and regulatory provisions in force (articles L.1121-3 and R.5121-13 of the Public Health Code).

- 1. Source documents

Source documents, which are defined as any original document or object making it possible to prove the existence or accuracy of data or facts recorded during the [clinical study](http://134.157.220.13/urcest/sous_cadre.php?fich=Lexique/E.htm#essaiclinique), will be kept for 15 years by the investigator or by the hospital in the case of hospital medical records.

- 1. Data confidentiality

In accordance with the legal provisions adressing data confidentiality for persons responsible for research quality control (article L.1121-3 of the Public Health Code), in accordance with the legal provisions relating to the confidentiality of information adressing, especially, the nature of the products, the trials, the persons taking part in them and the results obtained (article R. 5121-13 of the Public Health Code), persons with direct access will take all necessary precautions to ensure the confidentiality of information relating to the trials, the persons taking part in them and, in particular, their identity and the results obtained.

These people, in the same way as the investigators themselves, are subject to professional secret (under the conditions defined by articles 226-13 and 226-14 of the French Penal Code).

During the research or at its conclusion, the data collected on the participants and transmitted to the sponsor by the investigators (or any other specialist) will be rendered anonymous.

Under no circumstances may the names or addresses of the persons concerned appear.

Only the first letter of the participant's surname and first name will be recorded, together with a coded number specific to the study indicating the order of inclusion of participants.

The sponsor will ensure that each person taking part in the research has given their written consent for access to individual data concerning them and strictly necessary for the quality control of the research.

1. Quality control and assurance

A Clinical Research Assistant (CRA) may be appointed by the sponsor. He or she will ensure that the study is carried out properly, that the data generated are collected in writing, documented, recorded and reported, in accordance with the Standard Operating Procedures implemented at the CHRU de Brest and in compliance with Good Clinical Practice and the current legislative and regulatory provisions.

The investigator and the members of his team agree to be available for Quality Control visits carried out at regular intervals by the CRA. During these visits, the following elements may be reviewed in accordance with the monitoring grade defined by the sponsor for the study:

- informed consent
- compliance with the study protocol and the procedures defined therein
- quality of the data collected in the observation book: accuracy, missing data, consistency of data with "source" documents (medical records, appointment books, original laboratory results, etc.)
- completion of questionnaires or scales

The investigators also agree to accept quality assurance audits by the sponsor and inspections by the competent authorities. All data, documents and reports may be the subject of audits and regulatory inspections, without the right to invoke medical confidentiality.

1. Ethical considerations
   1. Individual Protection Committee

The study protocol, information form and consent form will be submitted to the Comité de Protection des Personnes for approval. Notification of the CPP's favourable opinion will be sent to the study sponsor and the competent authority.

The trial will be performed in accordance with the recommendations guiding physicians in biomedical research involving human subjects adopted by the 18th World Medical Assembly (Helsinki, Finland, 1964 and later revisions), the Tri-Council Policy Statement and the ICH Guidelines.

- 1. Substantial modification

Any substantial modification made to the protocol by the investigator must be approved by the sponsor. Prior to implementation, the sponsor must obtain a favourable opinion from the CPP. If necessary, new consent will be obtained from the persons taking part in the research.

- 1. Participant information and consent

The investigator will inform each participant prior to inclusion in the trial, full and adequate verbal and written information regarding the objective and procedures of the trial and the possible risks involved, the necessary surveillance and safety measures, their right to refuse to participate in the study or the possibility of withdrawing at any time.

For people screened (the general population of the COB area), this information will be given orally and a general information letter such as a leaflet or flyer will be sent to them.

For people recruited with a moderate CVDR, all the information is given on an information and consent form given to the participant. The participant's free, informed and written consent will be obtained before definitive inclusion in the study by the trainer who will represent one of the 3 doctors declared as investigators. These community champions will all have received appropriate training, validated by a certificate giving them the authority of the declared investigators to present and sign the consent form.

A copy of the information and consent form signed by both parties will be given to the participant, and the trainer will keep a copy.

As this study is taking place in the general population, all the participants recruited will depend on the 3 declared investigators.

1. **Data recording and processing**
   1. Observation book electronic

All the information required by the protocol must be recorded in the observation books. Data should be collected as it is obtained and recorded explicitly in the notebooks. Any missing data should be coded.

This electronic observation book will be accessible via an Internet data collection medium provided to community champions.

If the research team fills in the case report form via the Internet, the CRA can view the data quickly and remotely. The investigator is responsible for the accuracy, quality and relevance of all data entered. In addition, when data is entered, it is immediately checked for consistency. As such, he must validate any change in value in the CRF. These changes are subject to an audit trail. A justification may be included as a comment.

A pdf copy of the observation notebooks signed by the investigator will be saved and given to the investigator for archiving.

- 1. Data input and output

Data will be entered electronically via the web browser RedCap.

- 1. Data protection authority (CNIL)

As this study requires the community champions to contact patients with moderate cardiovascular risk at the end of the screening period, it is necessary for the research team to have the full identity of the participants, as well as their telephone and postal contact details. This identifying data, which is strictly necessary for carrying out the research, will be kept only until the end of the study and will be accessible only by the research staff. The "Reference Methodology" (MR-001 - N°1749494v0 dated 11/03/2014) in application of the provisions of article 54 paragraph 5 of law n°78-17 of 6 January 1978 as amended therefore applies to this project.

- 1. Archiving

All study data will be stored in the investigating centers and on the sponsor's premises in accordance with the current regulations.

1. Insurance

The Sponsor will take out insurance covering its own civil liability and that of any doctor involved in carrying out the study, for the entire duration of the study. It will also provide full compensation for the harmful consequences of the research for the person who takes part in it and their dependants, unless it can prove that the damage is not attributable to its fault or to that of any other party involved, without any claim being made against it on the grounds of a third party or the voluntary withdrawal of the person who initially agreed to take part in the research.

1. Feasibility

